**Methods:**

The trial is a single-center block randomized, controlled, observer-blinded, superiority and explorative trial with two parallel groups. The population consists of 200 older patients admitted to the ED: 70 patients without malnutrition or risk of malnutrition and 130 patients with or at risk of malnutrition defined as a Mini Nutritional Assessment-Short Form score ≤11. All patients without the risk of malnutrition receive the MED intervention, which consists of a medication review by a pharmacist and geriatrician in the ED. Patients with or at risk of malnutrition receive the MULTI-NUT-MED intervention, which consists of the MED intervention in addition to, dietary counseling and individualized interventions based on the results of screening tests for dysphagia, problems with activities of daily living, low muscle strength in the lower extremities, depression, and problems with oral health. Baseline data are collected upon study inclusion, and follow-up data are collected at 8 and 16 weeks after discharge. The primary outcomes are (1) change in medication appropriateness index (MAI) score from baseline to 8 weeks after discharge, (2) accuracy of different eGFR equations compared to mGFR, and (3) change in health-related quality of life (measured with EuroQol-5D-5L) from baseline to 16 weeks after discharge.

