#### Accuracy of estimated glomerular filtration rate in older medical patient

Another challenge during medication optimization is the accurate assessment of renal function [37, 38]. This is important because approximately 40% of all medications require dose adjustment according to renal function [39]. In clinical practice, renal function is typically determined with estimated glomerular filtration rate (eGFR) based on the measurement of serum creatinine. However, serum creatinine is heavily dependent on non-GFR determinants such as muscle mass, nutritional status, and sex, which can result in inaccurate eGFR and, therefore, inappropriate prescribing of renally cleared medications among older patients [40, 41]. Alternative markers of kidney function such as cystatin C, beta-trace protein (BTP), and beta-2-microglobulin (B2M) are less dependent on muscle mass, age, and sex compared to serum creatinine and may be more appropriate in older patients [40–42]. However, these novel biomarkers may be affected by other non-GFR determinants, such as inflammation, and there is a lack of knowledge regarding their impact among acutely admitted older patients [40, 41]. Therefore, we aim to determine which kidney marker or combination of markers is most accurate for older medical patients, as well as the impact of non-GFR determinants on this accuracy.

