### Aims

The study involving acutely admitted older medical patients has three primary aims (1) to determine whether a medication review intervention is superior to standard care in improving medication appropriateness from admission to 8 weeks after discharge, (2) to determine the accuracy of eGFR equations based on various biomarkers compared to mGFR at a single-time point, and (3) to determine whether an individualized multimodal and transitional nutritional intervention is superior to standard care in improving the quality of life from admission and 16 weeks after discharge.

The study also has the following secondary aims which are related to the effect of the intervention: (1) to measure differences in polypharmacy, PIM use, and assessment of underutilization between the MED-intervention and standard care from admission to 8 weeks after discharge and (2) to measure of the differences in body weight, protein- and energy intake, mobility, cognition, frailty, the intestinal microbiome, and health care costs between the MULTI-NUT-MED intervention and standard care from admission to 8 and 16 weeks after discharge and 1 year after discharge (only health care costs).

Secondary aims, which are based on baseline data or data from the control group, include assessment of (1) how information from a broad pharmacogenetic test can potentially improve medication prescribing appropriateness; (2) how polypharmacy, PIMs, nutritional status, frailty, and inflammation modify the effect of the MED-intervention on prescribing appropriateness; (3) how non-GFR determinants affects eGFR and how the choice of eGFR equation affects medication prescribing; (4) how the choice of malnutrition classification criteria affects the prevalence of malnutrition; and (5) how different definitions of frailty affect the distribution of patients classified as frail or sub-frail as well as the responsiveness of these methods.

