Intestinal microbiome	All participants at risk of malnutrition or with malnutrition according to the nutritional screening tool MNA-SF will collect a fecal sample using EasySampler [129]. Samples collected during hospitalization are frozen as fast as possible at −80°. If collected in the home of the participant, the sample is frozen as fast as possible in the participants own −18° freezer for maximally 3 days. The samples are transferred in a cooler bag with freezer elements to the −80° freezer (Biobank). At the time of collection, the participant reports where the sample belongs on the Bristol Stool Scale [130] and their use of antibiotics.	t_1_, t_2_, t_3_
Blood samples	Blood samples are analyzed for: Alanine aminotransferase, albumin, basic phosphatase, bilirubin, carbon dioxide, C-reactive protein, hemoglobin, coagulation factors II, VII, and X International Normalized Ratio, potassium, urea, coagulation factors, leukocytes, neutrophils, mean corpuscular hemoglobin concentration, mean cell volume, sodium, platelets, lactate dehydrogenase, neutrophil gelatinase-associated lipocalin, BTP and B2M, soluble urokinase plasminogen activator receptor, cholesterols, triglycerides, blood sugar, glycated hemoglobin, insulin, markers of the effect, and plasma levels of medication. Calculation of eGFR will be based on the Chronic Kidney Disease Epidemiology Collaboration [131–133], Berlin Initiative Study [132], Full Age Spectrum [42, 134, 135], Lund-Malmö revised [136], the Caucasian and Asian pediatric and adult subjects [137], Modification of Diet in Renal Disease [138], and Cockcroft-Gault [42] equations based on creatinine, cystatin C, B2M or BTP, or a combination of the markers.	t_1_, t_2_, t_3_, t_GFR_
Health economics	Use of health care services will be collected from the following registries: National Patient Registry, National Health Insurance Registry, The Danish National Prescription Registry [139], and local databases in the municipalities.	t_1-_ t_3_ and t_1_-t_1y_
Descriptive variables	Participant characteristics are based on participant self-report or obtained from the medical journal and include sex, age, civil status, living conditions, education, smoking status, alcohol consumption, physical activity level, use of home- and health care, early warning score and diagnoses.	t_1_

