### Sample size

The trial has three primary endpoints that build on mutually independent hypotheses [140]. Therefore, sample size calculations were performed for each endpoint as described below. All sample size calculations are performed for a significance level of 5%, power of 80%, and a dropout rate of 25%. Ethical approval was obtained for the inclusion of 200 participants in total to ensure enough power for all primary endpoints.
1: Based on a *t* test, a sample size of 120 is required to detect a clinical difference of 3 points (SD=5 points [36]) in MAI score change from baseline to 8 weeks after discharge between the control group and pooled intervention group (MED and MULTI-NUT-MED intervention).2: Based on a paired *t* test, a sample size of 62 participants is required to detect a clinically relevant difference of 4.0 mL/min/1.73m^2^ (SD=15, a R=0.73 [141]) between mGFR and eGFR based on the combination of creatinine and cystatin C. GFR is measured at baseline for all trial participants regardless of group allocation.3: Based on a *t* test, a sample size of 130 participants with or at risk of malnutrition is required to detect a clinically relevant difference of 0.15 points [142] (SD=0.27 [143]) in EuroQol-5D-5L score change from baseline to 16 weeks after discharge between the control group and MULTI-NUT-MED intervention group, assuming equal allocation in the two groups.

Given that patients are included independently of nutrition status and approximately 70% of patients are expected to have or be at risk of malnutrition [4], a total of 185 participants is required to achieve a sample size of 130 participants with or at risk of malnutrition.

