### Statistical methods

#### Primary outcomes

Differences in MAI score, change from baseline to 8 weeks after discharge between the control group and pooled intervention group (MED and MULTI-NUT-MED intervention), will be evaluated by analysis of covariance (ANCOVA). The primary analysis will model the randomization group and baseline MAI-score as independent variables by the intention-to-treat principle. Additional analyses will be adjusted for potential confounders that are unequally distributed between groups despite randomization. Missing data on the primary end point will be accounted for by multiple imputations using the PROC MI procedure with fully conditional specification (FCS) and a minimum of 100 imputations. Imputation will use earlier measurements of the imputed outcome, number of medications, and randomization group, along with age and sex for prediction models.

Differences between mGFR and eGFR based on both the combination of creatinine and cystatin C will be evaluated by mixed linear regression analysis.

The difference in EuroQol-5D-5L score change from baseline to 16 weeks after discharge between the control group and MULTI-NUT-MED intervention group will be evaluated by ANCOVA. The primary analysis will model randomization group and baseline EuroQol-5D-5L as independent variables with either intention-to-treat analysis or per-protocol analysis, where participants are considered compliant if they received and were compliant to at least one intervention if one was recommended, two if two were recommended, two if three were recommended, three if four were recommended, and four if five or six were recommended. Additional analyses will be adjusted for potential confounders that are unequally distributed between groups despite randomization. Missing data on the primary endpoint will be accounted for by multiple imputations using the PROC MI procedure with fully conditional specification (FCS) and a minimum of 100 imputations. Imputation will use earlier measurements of the imputed outcome along with age, sex, and diagnosis codes for prediction models.

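### Primary outcome 2 is the accuracy of several eGFR equations, but the stated primary analysis and sample size cover only the mean difference from mGFR for creatinine plus cystatin C

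*Protocol article*

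**What the plan says.** The outcome is described in the plural. The Abstract (Methods) gives primary outcome 2 as "accuracy of different eGFR equations compared to mGFR". The Aims section sets out "to determine the accuracy of eGFR equations based on various biomarkers compared to mGFR at a single-time point". The Introduction, in its subsection on eGFR in older patients, goes further and adds a comparison: "we aim to determine which kidney marker or combination of markers is most accurate for older medical patients".

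Table 2 (blood samples row) names seven equations or equation families, to be calculated as "equations based on creatinine, cystatin C, B2M or BTP, or a combination of the markers".

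The analysis is described in the singular. Under Statistical methods, Primary outcomes, the whole entry for this outcome is: "Differences between mGFR and eGFR based on both the combination of creatinine and cystatin C will be evaluated by mixed linear regression analysis". The Sample size section powers the same contrast, "between mGFR and eGFR based on the combination of creatinine and cystatin C", by a paired t test with a difference of 4.0 mL/min/1.73 m2, SD 15 and R 0.73, and arrives at 62 participants.

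Two related analyses appear under Secondary outcomes: a linear regression of the mGFR–eGFR difference on non-GFR determinants, and kappa for agreement on chronic kidney disease class.

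**The concern.** There are two gaps between what is promised and what is fixed.

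- **Scope.** The outcome covers several equations on four markers, alone or combined. The primary analysis covers one combination. Single-marker equations, and anything using B2M or BTP, are outside it, and no comparison between equations is stated anywhere.
- **Quantity.** The sample size is for a mean difference. Over- and underestimation cancel in a mean, so an estimator with wide individual error can show no bias. No primary measure of spread or of individual accuracy is stated.

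The Introduction motivates this aim by dose adjustment to renal function, which depends on how far the estimate is off in the individual patient. A primary result that describes only the average error of one marker combination would leave that question, and the question of which marker does best, without a prespecified answer.

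**Working it through.** **Inputs (Sample size section):** difference 4.0 mL/min/1.73 m2; SD 15; R 0.73; alpha 5%; power 80%; dropout 25%; stated n = 62.

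**Step 1. Reproduce the stated figure.** Taking 15 as the SD of each measurement:

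SD of differences = 15 × √(2 × (1 − 0.73)) = 15 × √0.54 = 11.02.

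A two-sided paired t test for a mean difference of 4.0 needs n = 61.55, rounded up to 62, with power 80.3% at 62. The stated figure reproduces. Two other readings were tried:
- Treating 15 as the SD of the differences gives 113, which does not match.
- A one-sided test gives 49, and 49 × 1.25 = 61.25 also rounds up to 62.

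Both readings that reach 62 size a test of one mean difference.

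**Step 2. What that design measures well, and what it does not.** At n = 62 the 95% confidence interval for the mean difference has half-width 2.00 × 11.02/√62 = 2.8 mL/min/1.73 m2. The spread of individual differences is much larger: 95% limits of agreement = bias ± 1.96 × 11.02 = bias ± 21.6. At zero bias they run from −21.6 to +21.6.

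**Step 3. Bias and accuracy can order estimators differently.** This is an illustration only. It assumes mGFR 60, so that 30% is 18 mL/min/1.73 m2, and normally distributed differences.

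| Bias | SD of differences | Share within 30% of mGFR |
|---|---|---|
| 0 | 5 | 99.97% |
| 0 | 11.02 | 89.8% |
| 0 | 20 | 63.2% |
| 4 | 5 | 99.7% |

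Judged by mean difference, the third row beats the fourth. Judged by the share of patients estimated within 30%, the fourth is far better.

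**Step 4. Do the secondary analyses fill the gap?** The regression on non-GFR determinants explains what drives the difference; it does not summarise its size for each equation. Kappa on disease class measures agreement on a categorised scale. Neither is primary, and neither is stated to rank the equations.

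**The case against.** The strongest objection is that this is detail for a statistical analysis plan. The article is condensed, no SAP is shown, and the choice of P30 or limits of agreement is commonly left there. That is right about the particular metrics, and their absence alone would not be a finding. It does not remove the mismatch, because the article does not defer the matter: it states a primary analysis and a sample size, and these do not match its own primary outcome.

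A second objection is that a mixed linear regression can yield a residual spread and can handle several estimates per patient. It can, but the article names neither as a target, and the quantity it powers is a mean difference.

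Several stronger readings are tempting, and the text does not support them:
- A reader might infer that only one equation is analysed. The text names one marker combination, which more than one listed equation could use, and the sentence is garbled enough that words may be missing.
- A reader might infer that a non-significant result will be taken as proof of accuracy. No section sets such a rule.
- A reader might treat 4.0 as a tolerance for individual patients, or as an equivalence margin, and conclude that most patients would be misestimated. The Sample size section uses 4.0 only as a group mean difference. At an assumed mGFR of 60 and zero bias, the plan's own SD puts about 90% of estimates within 30% of mGFR.
- A reader might say that primary aim 2 is to find the best equation for prescribing. The Aims section speaks only of determining accuracy. The search for the most accurate marker is in the Introduction, and the effect of equation choice on prescribing is a separate secondary aim.

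**Conclusion.** The mismatch is real and should be corrected before analysis. The primary analysis and the n = 62 address mean bias of the creatinine plus cystatin C combination. Primary outcome 2 concerns the accuracy of several equations, and the remaining markers and equations in Table 2 have no stated primary analysis.

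The size of what a mean leaves out is shown by limits of agreement of about ±21.6 mL/min/1.73 m2 at zero bias. This rests on the plan's SD of 15 applying to both measurements, its R of 0.73, and roughly normal differences. It says nothing about whether any equation will prove accurate or inaccurate in this population. The point is that the analysis as written would not show it.

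**What to change.** In Statistical methods, Primary outcomes, replace the single sentence for this outcome with the following:

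1. For every equation listed in Table 2, calculated from the blood sample taken at the GFR measurement (t_GFR), report bias, precision (SD of differences and limits of agreement) and P30, each with a 95% confidence interval. Table 1 allows t_GFR to fall up to 2 weeks after discharge, so the baseline sample is not a substitute.
2. Compare equations within patient on P30 and absolute error against one creatinine-only reference equation, named in advance. Either control for multiplicity or label these comparisons as estimation.
3. In Sample size, state that the 62 applies only to mean bias of the creatinine plus cystatin C combination.

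**Cost.** The change is to wording and analysis only: the equations and the t_GFR samples are already planned. There are more estimates to report, and the stated power no longer describes the main measure. Precision for P30 is limited. Assuming P30 near 80% (not a figure from the article), the 95% half-width is 1.96 × √(0.8 × 0.2/n). This is about 10 points at n = 62 and about 9 points at n = 83, where 83 is 62/(1 − 0.25), the stated size inflated for the plan's 25% dropout.

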### Standard care

The intervention is given in addition to standard care. The control group is offered standard care only. Standard care was chosen as the comparator as this is what needs to be improved.

Medication reconciliation is performed by a clinical pharmacist within 24 h of ED admission for all patients [61]. If available, an initial medication list is obtained from the admitting ED physician. This initial list is compared with the hospital’s electronic patient record system and Shared Medication Card, a central containing information about all medications prescribed and dispensed within the previous 2 years [62]. Each participant is then asked to confirm the use of each medication. If a participant is unable to provide reliable information, then the medication list is confirmed with a caregiver (e.g., family member, GP, home nurse, nursing home staff, or community pharmacy). The final medication list is documented in the electronic patient record along with any discrepancies between the initial and final medication list. The final medication list is communicated to the providing geriatrician, who updates the participant’s electronic prescriptions accordingly.

According to the regional nutritional guideline in the Capital Region of Denmark, all patients with an expected hospital stay of more than 24 h should be screened for nutritional risk during the first 24 h of hospitalization and have treatment initiated when relevant [63]. All trial participants are offered the same foods and nutritional products during hospitalization, except for the protein supplement P-Boost®, which is only offered to participants in the intervention group (see the “Dietary Counseling” section).

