#### Compliance

Participant compliance is defined separately for each element of the intervention. Compliance to medication review is defined as having received a medication review that is evaluated and effectuated by a geriatrician. Compliance with dietary counseling is defined as having counseling during hospitalization and ≥3 home visits after discharge. Compliance with physiotherapy is defined as having received ≥75% of training sessions. Compliance with occupational therapy is defined as having received ≥75% of the home visits for dysphagia and ≥75% of home visits for ADL if deemed relevant by the occupational therapist. Compliance to evaluation and treatment of depression is defined as having received an evaluation by the geriatrician. Compliance with oral health-related intervention is defined as having received an evaluation by a dentist and ≥1 home visit by a dental hygienist if deemed relevant by the dentist.

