### Blinding

The nature of the intervention does not allow blinding of participants or personnel performing the intervention. However, the outcome assessor is blinded to the result of the randomization throughout the trial, and all data analysis is performed blinded.

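### The primary EuroQol-5D-5L analysis may be intention-to-treat or per-protocol, with no rule for choosing, and the per-protocol rule can exclude intervention patients only

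*Protocol article*

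**What the plan says.** All references are to the protocol article.

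- **Statistical methods, Primary outcomes, EuroQol-5D-5L.** The primary ANCOVA takes randomisation group and baseline score "as independent variables with either intention-to-treat analysis or per-protocol analysis". The per-protocol set follows: "participants are considered compliant if they received and were compliant to at least one intervention if one was recommended, two if two were recommended". The required count continues as two of three, three of four, and four of five or six.
- **Same section, MAI.** "The primary analysis will model the randomization group and baseline MAI-score as independent variables by the intention-to-treat principle". Only one population is named.
- **Compliance.** "Participant compliance is defined separately for each element of the intervention". For example: "Compliance with dietary counseling is defined as having counseling during hospitalization and ≥3 home visits after discharge".
- **Standard care.** "The control group is offered standard care only".
- **Aims.** The quality-of-life aim is superiority over standard care at 16 weeks.
- **Blinding.** Participants and treating staff are unblinded, the outcome assessor is blinded, and "all data analysis is performed blinded".

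**The concern.** A primary analysis needs one named population. Here the text addresses the question, sets out a detailed per-protocol rule, and still leaves two populations open for one of three primary endpoints. It does not say which carries the claim, how the choice is made, or when.

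The two populations are not interchangeable. Intention-to-treat compares the groups that randomisation formed. The per-protocol rule, as written, compares a subset of the intervention arm, selected on what happened after allocation, with a control arm to which the rule cannot be applied. Any link between compliance and prognosis then enters the estimated effect. At stake are the type I error of the quality-of-life claim and whether its estimate can be read as an effect of the intervention.

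**Working it through.** **1. The plan's own figure.** From Sample size: difference 0.15, SD 0.27, significance level 5% (taken as two-sided), power 80%, dropout 25%, equal allocation.

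- Normal approximation: n per arm = 2 × (1.96 + 0.84)² × 0.27² / 0.15², rounded up to 51. The t-test solution is 51.8, so 52.
- 2 × 52 = 104, and 104 × 1.25 = 130. The stated 130 is reproduced.
- After 25% dropout, 130 × 0.75 = 97.5 remain, or 48.75 per arm. The calculations below use 49 in the simulation and 48.75 for power.

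**2. Whom the per-protocol rule can exclude.** It counts recommended trial elements complied with. Controls are recommended none. Applied literally to controls it has no content, so the workable reading keeps all controls and drops intervention patients who fall short.

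**3. Bias of that comparison with no treatment effect.** Let q be the non-compliant fraction and g the amount by which non-compliers' change is worse, whatever the treatment. Both are assumptions; the article gives neither.

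- The control mean lies q × g below the complier mean, so the per-protocol bias is q × g.
- q = 0.30, g = 0.10: 0.30 × 0.10 = +0.03, which is 20% of 0.15.
- q = 0.30, g = 0.20: 0.30 × 0.20 = +0.06, which is 40% of 0.15.
- If non-compliers do better, the sign reverses.

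**4. Type I error if either population may carry the claim.** Simulation: 40,000 trials, 49 per arm, SD 0.27, no treatment effect, two-sided unadjusted t tests at 5%. Per-protocol is intervention compliers against all controls. Intention-to-treat alone rejects in 4.8–5.1% of trials.

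| Non-compliance | Either significant, g = 0 | Either significant, g = 0.135 (0.5 SD) | Per-protocol bias at g = 0.135 |
|---|---|---|---|
| 10% | 6.0% | 6.8% | +0.014 |
| 25% | 6.8% | 10.6% | +0.034 |
| 40% | 7.1% | 15.0% | +0.054 |
| 50% | 7.7% | 18.7% | +0.068 |

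Over 20–40% non-compliance with g = 0, the error is about 6.5–7%. At 30% non-compliance with g = 0.10 to 0.20, it is about 10–18%. A repeat run for this write-up gave the same figures to within simulation error.

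**5. Power.** Per-protocol also loses patients. With SE = 0.27 × √(1/48.75 + 1/(48.75c)) for compliance c, and power = Φ(0.15/SE − 1.96):

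- c = 1 (intention-to-treat): 78.3%
- c = 0.75: 71.9%
- c = 0.60: 66.1%

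**The case against.** **The sentence may be loose drafting for running both analyses, and a fuller document may rank them.** This is possible. The compliance thresholds are fixed in advance, so the per-protocol set is not itself improvised. But the text goes beyond silence: it describes the primary analysis as one or the other, next to an MAI paragraph that names a single population. It needs correcting on its face.

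**A reader might infer that the population will be picked once the results are known.** The article does not say so. It leaves that possible by giving no rule or time. Blinded analysis is a partial safeguard: a blinded analyst can still see which population is significant, and exclusions falling on one coded arm tend to reveal that arm. Any per-protocol analysis has this unmasking problem, including a supportive one, so it is an argument about order of analysis rather than a separate fault.

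**A reader might infer that compliers are the fitter patients, for instance because they completed training sessions.** The documents do not support this as fact.

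- Physiotherapy is reached only through low Functional Recovery Score items, which also trigger the activities-of-daily-living intervention, and dietary counselling is part of the package. Such patients have at least three elements and need two of three (or three of four, or four of five or six). One can miss all training and still count as compliant.
- Several elements turn on a geriatrician's or dentist's action rather than on patient fitness.
- The rule is strictest for patients with one or two recommended elements, which could retain sicker patients with more.
- Patients who recover quickly may decline visits.

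These points stand, so the direction is plausible at most. They do not restore the randomised comparison.

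**The larger error rates depend on assumptions.** This stands too. The planned ANCOVA would absorb whatever part of a prognostic gap is visible at baseline; the simulation did not adjust for it. Only the 6.5–7% figure needs no prognostic gap, and it still assumes a non-compliance rate.

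**The article does not say how controls enter the per-protocol set.** True, and municipal standard care can include dietetic advice. But the written rule counts recommended trial elements and offers no counterpart for controls.

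**Conclusion.** The point holds in this form: the primary EuroQol-5D-5L population is left open between two options, one of which, as written, drops patients from the intervention arm only, on a post-randomisation criterion. Following the text, a superiority claim could rest on a non-randomised comparison. That is more than omitted detail.

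Allowing a claim on either population takes the 5% error to about 6.5–7% at an assumed 20–40% non-compliance, with compliance unrelated to prognosis. The range of about 10–18%, with bias of about +0.03 to +0.06 against 0.15, is an illustration: it assumes 30% non-compliance, non-compliers 0.10–0.20 worse, and no baseline adjustment. The documents give no compliance rate or prognostic gap and do not establish the sign of the bias. It would plausibly favour the intervention if compliers have the better prognosis.

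**What to change.** Replace the open choice with a statement that the sole primary EuroQol-5D-5L analysis is intention-to-treat: all randomised patients with MNA-SF ≤11, analysed as allocated, on the same principle as MAI. Label the per-protocol analysis as supportive, run after the blinded intention-to-treat result is fixed, and not a basis for the superiority claim.

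The cost is one or two sentences in the protocol or analysis plan. The sample size stays at 130 and no further data are needed.

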All additional confirmative outcomes will be evaluated by *t* test, Kruskal-Wallis test, chi-square test, two proportions *z* test, or Friedman’s analysis of variance depending on the distribution of the relevant variable. The analysis will be adjusted for multiple testing. Associations between variables will be evaluated by adjusted multiple regression models, and repeated measurements will be evaluated by mixed models of paired *t* tests or Fisher’s exact test. Missing data on secondary endpoints will be accounted for with multiple imputations as previously described.

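### The stated imputation model for the primary EuroQol-5D-5L outcome omits randomisation group, so imputed week-16 scores carry no treatment effect beyond what observed earlier scores carry, and the estimate is pulled toward zero

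*Protocol article*

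**What the plan says.** All of this is in the protocol article, under Statistical methods.

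- **Analysis model, EuroQol-5D-5L (Primary outcomes):** "The primary analysis will model randomization group and baseline EuroQol-5D-5L as independent variables with either intention-to-treat analysis or per-protocol analysis". Group is the term that gives the treatment effect.
- **Imputation method, both outcomes:** "multiple imputations using the PROC MI procedure with fully conditional specification (FCS) and a minimum of 100 imputations".
- **Predictors for MAI:** "Imputation will use earlier measurements of the imputed outcome, number of medications, and randomization group, along with age and sex for prediction models".
- **Predictors for EuroQol-5D-5L:** "Imputation will use earlier measurements of the imputed outcome along with age, sex, and diagnosis codes for prediction models".
- **Secondary endpoints (Secondary outcomes):** "Missing data on secondary endpoints will be accounted for with multiple imputations as previously described".

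No section says that imputation is done separately by arm. Tables 1 and 2 schedule EuroQol-5D-5L at baseline, 8 weeks, 16 weeks and 1 year. The earlier measurements available for week 16 are therefore baseline and, where observed, week 8.

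**The concern.** An imputation model should contain at least the variables of the analysis it feeds. Here the analysis estimates a group effect, and the imputation model is told nothing about group. The missing week-16 scores of both arms are drawn from one common regression, so the arm difference among imputed participants can come only from their earlier scores. Baseline carries no arm difference, because of randomisation. Week 8 carries one only if it was observed and the intervention had already worked by then.

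If the intervention works, the estimate is diluted even when data are missing completely at random. Running 100 imputations instead of 20 does not help, because every draw comes from the same misspecified model. At stake are the size of a primary effect and the power to detect it, in a trial that plans for 25% dropout.

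This is not a detail that an article leaves to a fuller document. The article gives a predictor list for each of the two outcomes, and only one list names group.

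**Working it through.** **Inputs from the Sample size section.** The trial is to "detect a clinically relevant difference of 0.15 points [142] (SD=0.27 [143]) in EuroQol-5D-5L score change from baseline to 16 weeks after discharge", and "All sample size calculations are performed for a significance level of 5%, power of 80%, and a dropout rate of 25"%. N = 130 with equal allocation. A two-sided test is assumed, as sidedness is not stated.

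**The plan's own figure.** A two-sample t test with difference 0.15 and SD 0.27 needs 51.84, so 52, per arm: 104 in total, and 104 × 1.25 = 130. The stated size is reproduced.

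**Assumptions not in the document.** SD 0.27 at each visit; correlation 0.5 between baseline and each follow-up, so the SD of change is 0.27 × √(2 × (1 − 0.5)) = 0.27; correlation 0.6 between weeks 8 and 16; missing completely at random; true week-16 effect δ = 0.15; week-8 effect d between 0 and 0.15.

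**Week 8 also missing.** Let the control mean be c. Completers are half treated, so both arms are imputed around c + δ/2.

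- Treated mean: (1 − m)(c + δ) + m(c + δ/2)
- Control mean: (1 − m)c + m(c + δ/2)
- Difference: (1 − m)δ = 0.75 × 0.15 = 0.1125, which is 75% of the true effect

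**Week 8 observed in everyone.** The pooled regression of week 16 on baseline and week 8, without group, has week-8 slope

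b = [(0.6 − 0.5²)σ² + dδ/4] / [(1 − 0.5²)σ² + d²/4], with σ² = 0.27² = 0.0729.

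The difference is (1 − m)δ + m·b·d.

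- d = 0.15: b = (0.025515 + 0.005625)/(0.054675 + 0.005625) = 0.516; difference = 0.1125 + 0.25 × 0.516 × 0.15 = 0.132 (88%)
- d = 0.075: b = (0.025515 + 0.0028125)/(0.054675 + 0.00140625) = 0.505; difference = 0.1125 + 0.25 × 0.505 × 0.075 = 0.122 (81%)
- d = 0: difference = 0.1125 (75%)

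The same formulas keep 85% to 93% of the effect at 15% missing and 65% to 83% at 35% missing. Large-sample simulation (N = 100,000) agrees to within about one percentage point, and adding group restores about 0.15 in every scenario.

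**At trial size.** N = 130, 25% missing, 1,000 replicates, 20 imputations:

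| Week-8 effect | Share of dropouts with week 8 | Mean estimate, without / with group | Power, without / with group |
|---|---|---|---|
| 0.075 | 0% | 0.112 / 0.147 | 0.673 / 0.857 |
| 0.075 | 50% | 0.118 / 0.151 | 0.757 / 0.878 |
| 0.075 | 100% | 0.123 / 0.150 | 0.790 / 0.876 |
| 0.15 | 0% | 0.111 / 0.151 | 0.680 / 0.865 |
| 0.15 | 50% | 0.124 / 0.150 | 0.794 / 0.883 |
| 0.15 | 100% | 0.130 / 0.153 | 0.855 / 0.900 |

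A separate run of 800 replicates gave power 0.87 against 0.89 in the most favourable case and 0.67 against 0.88 in the least favourable. The Monte Carlo error of one such power is about √(0.87 × 0.13/1000) = 0.011, so the two runs are compatible. The loss is about 2 to 20 percentage points.

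**Standard errors.** Without group, the average combined standard error is 0.046 to 0.048, while the estimates vary with an empirical standard error of only 0.035 to 0.039. With group, the two agree (about 0.047 to 0.048 each). With no true effect, the model without group gives no bias and a type I error of about 1%, below the nominal 5%.

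**The case against.** The strongest reply is that the size depends on the scenario and that the protocol protects this outcome. EuroQol-5D-5L is measured at week 8, and the imputation uses earlier scores. Under Data collection methods it is part of the minimal data set offered to participants who decline full follow-up, and components that can be done by telephone are offered after that. The 25% is a generic planning rate for dropout, not a forecast of missing EuroQol-5D-5L data. With 10% missing and week 8 observed with the full effect, the estimate is 0.143 without group against 0.150 with it, and power is equal. This stands: it limits the size but does not remove the bias.

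Four stronger readings are tempting but not supported:

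- *Imputed values carry no treatment effect at all.* This holds only where week 8 is missing or shows no effect.
- *The trial could produce a false benefit.* The error runs the other way: estimates shrink and standard errors are too large.
- *Secondary endpoints are also imputed without group.* The reference back does not say which of the two differing lists applies, and AOU is to be analysed like MAI, whose list includes group. This is an ambiguity, not a shown omission.
- *Other analysis variables are missing, or the diagnosis codes are unusable.* Baseline EuroQol-5D-5L is already an earlier measurement. Municipality (a stratification factor) and MNA-SF (which defines the subgroup) are not terms in the primary ANCOVA. Nothing says that the codes enter uncollapsed, so recoding them is a preference.

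An analysis plan that is not shown might add group or impute by arm. The article nevertheless states a list, and an analyst following it would leave group out.

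**Conclusion.** The point holds in this form. The stated EuroQol-5D-5L imputation model omits randomisation group, which the MAI model includes and the EuroQol-5D-5L ANCOVA needs. At 25% missing, a true 0.15 is estimated as about 0.11 to 0.13, an attenuation of 12% to 25%. Power falls by about 2 to 20 percentage points. In the less favourable scenarios it drops below the planned 80% because of the imputation list alone.

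These sizes rest on the assumed correlations of 0.5 and 0.6, a week-8 effect between none and the full 0.15, and data missing completely at random. The direction was toward zero in every scenario examined. The error is conservative, but in a superiority trial it can hide a real benefit, and it misstates a primary estimate.

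**What to change.** Add randomisation group to the EuroQol-5D-5L imputation model, as is already done for MAI, or impute separately by arm. State under Secondary outcomes that the imputation model for those endpoints also includes group, so that the reference back is no longer open to two readings.

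The cost is one term in the PROC MI specification and one sentence of text. No new data are needed, and the sample size does not change. The change should be recorded before the analysis is run.
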